## Abstract

**Background:**

Organization, time management, and planning (OTMP) difficulties are associated with academic underachievement. OTMP skills training programs are effective in reducing OTMP deficits and improving academic performance. A randomized controlled trial of Homework, Organization, and Planning Skills (HOPS) for students ages 11–14 found it to be effective with medium to large effects. In that study, HOPS was provided by counselors employed by the research team. This study is a replication examining HOPS under more authentic conditions when providers are employed by schools serving enrolled students. The primary aim is to evaluate HOPS offered by school providers in relation to treatment-as-usual/waitlist (TAU/WL). To respond to limited school resources post-COVID-19, HOPS is also provided by research team members, creating the opportunity to replicate the findings from the prior trial and explore differential effectiveness when HOPS is implemented by school vs. research providers.

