### Prior research on HOPS program

In an early study of HOPS, the program was implemented by school mental health professionals in participating schools to 47 students identified as having ADHD and academic problems [10]. The study showed that school counselors demonstrated a high level of fidelity to intervention content. In comparison to a treatment-as-usual, waitlist (TAU/WL) control condition, caregivers in HOPS reported their children made significant improvements in organized actions (Cohen’s *d* = 0.88), task planning (*d* = 1.05), and homework completion behaviors (*d* = 0.85). Outcomes based on teacher ratings did not show improvement. Gains based on caregiver ratings generally were maintained at 3-month follow-up. In addition, HOPS participants demonstrated a superior grade point average (GPA) in comparison to TAU/WL.

HOPS was evaluated subsequently in a large-scale randomized controlled trial (RCT, *n* = 280, 7 schools; [4]). The trial was conducted in authentic practice settings (schools). Intervention providers were school counselors who had recently graduated, but they were hired and supervised by the research team. The findings revealed that, compared to TAU/WL, students receiving HOPS demonstrated significant improvements with large effect sizes in caregiver ratings of homework performance (*d* = 1.29), task planning (*d* = .79), materials management (*d* = .81), and organized actions (*d* = 1.14). Improvements based on teacher ratings were significant with medium effect sizes in materials management (*d* = .53) and organized actions (*d* = .55). Findings showed evidence of sustained effects when assessed about 3 months after intervention. An examination of implementation factors revealed that counselor-reported working alliance was a significant predictor of favorable effects of HOPS on outcomes [11].

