#### Analyses for Aims 1–3: Evaluation of HOPS vs. TAU/WL and comparison of HOPS-ST to HOPS-RT.

*Hypothesis 1:* Students in HOPS-ST will demonstrate significantly fewer OTMP skills deficits and homework problems and will show significantly better academic performance at post-treatment compared to students in TAU-WL*Hypothesis 2:* Students in HOPS-RT will demonstrate significantly fewer OTMP skills deficits and homework problems and will show significantly better academic performance at post-treatment compared to students in TAU-WL.*Exploratory:* Examine whether the effects of HOPS-ST and HOPS-RT differ at post-treatment and follow-up.

A linear mixed-effects modeling approach will be used to examine intervention effects at post-treatment. An intent-to-treat approach to data analysis will be applied, including all children with baseline data in the analytic model. Under this approach, we will examine differences between students in HOPS (for HOPS-ST and HOPS-RT separately) vs. TAU-WL (as well as for students in HOPS-ST vs. HOPS-RT) by fitting a multilevel model in which students are nested within schools. In addition to including an indicator variable for the treatment condition, we will include covariates that explain variation at the student and school levels. To explore the sustainability of the intervention effect, we will examine how both means and slopes (rates of change) vary from baseline to 6-month and 12-month follow-up using regression analyses. Changes in mean and slope reflect variations in the magnitude of effect and pace of change during different phases of the study.

Because the efficacy of HOPS will be evaluated on three different domains of outcome measures (organizational skills, homework performance, academic achievement), we will use a Bonferroni-adjusted significance level to correct for multiple comparisons within each domain. As a result, the significance level will be adjusted to.025 per domain for the two measures of organizational skills (COSS-P, COSS-T), the two measures of homework performance (HPC, HPQ-T), and the two measures of academic achievement (APS, academic grades).

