Power calculations were based on the following design parameters: *N = 30* schools (20 assigned to HOPS, 10 assigned to TAU); ICC = 0.04 (based on [4]); α=0.025  (reflecting the Bonferroni corrected significance level to accommodate multiple testing of two outcomes for each outcome domain); and $R^{\text{2}}=\text{0}.\text{6}\text{0}$ at the student and school level (which is the proportion of variation in outcomes explained by student and school-level covariates). Based on initial projections, we expected to enroll 8 students per school for a total of 240 participants (216 with 15% attrition), which would be sufficient to identify a minimal detectable effect size (MDES) of 0.41. Because of recruitment challenges primarily due to barriers related to the COVID-19 pandemic, we adjusted these projections to an average of 4.5 students/school for 30 schools for a total of 135 participants (122 with attrition). This sample size will result in a MDES of 0.48 with adequate power (80%). Based on prior research by [name] and colleagues [4], the MDES for primary outcomes in our study is well within the range of expected effect sizes.

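### The multiplicity rule holds error at 5% within each outcome domain, not for an overall claim that HOPS-ST is effective, and Holm would be a more powerful rule within each domain

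*Protocol article*

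**What the plan says.** The Abstract (Background) names the main comparison: "The primary aim is to evaluate HOPS offered by school providers in relation to treatment-as-usual/waitlist (TAU/WL"). Aim 1 and Hypothesis 1 test it at post-treatment on organizational skills, homework performance and academic performance.

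The analysis section for Aims 1–3 gives the reason for a correction: "the efficacy of HOPS will be evaluated on three different domains of outcome measures (organizational skills, homework performance, academic achievement"). The remedy is narrower: "we will use a Bonferroni-adjusted significance level to correct for multiple comparisons within each domain". In numbers, "the significance level will be adjusted to.025 per domain for the two measures of organizational skills (COSS-P, COSS-T"), with the same level for "the two measures of homework performance (HPC, HPQ-T), and the two measures of academic achievement (APS, academic grades"). The power paragraph confirms the scope of the 0.025, described as "reflecting the Bonferroni corrected significance level to accommodate multiple testing of two outcomes for each outcome domain".

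The same paragraph concludes that "the MDES for primary outcomes in our study is well within the range of expected effect sizes". No section says which outcomes those are. Aim 1 and the outcome-measures section sort the measures into proximal and distal, but neither ranks them or orders the tests.

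**The concern.** The reason given and the remedy do not match. Three domains are cited as the source of multiplicity, yet the correction deals only with the two measures inside a domain. The primary contrast therefore has six tests at 0.025, and no statement of how they combine into an answer to Aim 1.

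A mixed result is a realistic prospect. For the early 47-student HOPS study the article reports gains on caregiver ratings, while "Outcomes based on teacher ratings did not show improvement". The larger trial (n = 280) did find teacher-rated effects (d = .53 and .55), so disagreement is possible but not certain. Without a stated reading, one positive measure out of six could be presented as showing that HOPS works when school staff deliver it, and that statement would not carry 5% error control.

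A smaller matter concerns the rule inside each domain. Single-step Bonferroni gives up power that a step-down rule would keep at the same error rate. Projected enrolment has already fallen from 240 to 135 students.

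**Working it through.** **Inputs from the article:** one primary contrast (HOPS-ST vs TAU/WL), three domains, two measures per domain, 0.025 per test.

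**Assumptions:** the article gives neither the sidedness of the tests nor the correlations between outcomes. I take two-sided tests and a common correlation r over a range. Results for r > 0 come from simulating multivariate normal test statistics.

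**1. The plan's own figure.** 0.05 / 2 = 0.025, which reproduces the stated level.

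**2. Error within one domain.** The Bonferroni bound is 2 × 0.025 = 0.05. With independent measures it is 1 − 0.975² = 0.0494. Each domain is held at 5% as intended.

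**3. Error over the six tests of the primary contrast, global null.** The bound is 6 × 0.025 = 0.15. With independent measures the rate is 1 − 0.975⁶ = 0.141. Counting only results that favour HOPS, each test has a 0.0125 chance of a false positive, and 1 − 0.9875⁶ = 0.073.

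| r | Any of six, either direction | Any of six, favouring HOPS |
|---|---|---|
| 0 | 14.1% | 7.3% |
| 0.2 | 13.5% | 6.8% |
| 0.5 | 11.2% | 5.6% |
| 0.8 | 7.6% | 3.8% |
| 0.9 | 5.8% | 2.9% |

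The benchmarks are 5% for the middle column and 2.5% for the right-hand one. Letting measures correlate more strongly within a domain than between domains changes little: 0.5 within and 0.3 between gives 12.5%; 0.7 within and 0.4 between gives 11.2%.

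**4. The opposite reading.** If Aim 1 succeeded only when every domain had at least one significant measure favouring HOPS, the false-claim rate would be about 0.2% or less for r up to 0.5. The result thus depends almost entirely on a decision rule that the article does not give.

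**5. Holm against Bonferroni inside one domain.** Assume that each measure has 80% power at two-sided 0.025. The mean of each test statistic is then 2.241 + 0.842 = 3.083. Take r = 0.5. Holm tests the smaller p at 0.025 and, if that is significant, the larger p at 0.05.

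| Power | Bonferroni | Holm |
|---|---|---|
| A given measure | 0.80 | 0.85 |
| Both measures | 0.69 | 0.78 |
| At least one measure | 0.91 | 0.91 |

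The last row cannot differ, because Holm's first step is the Bonferroni test. For the same reason Holm leaves every rate in step 3 unchanged.

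**The case against.** The strongest reply is that domain-wise families are a legitimate choice made in advance. The analysis and power paragraphs use the same definition. If the trial reports three separate domain conclusions, each is held at 5% and no further correction is needed. That stands. What is missing is a statement that conclusions will be drawn this way; the article also speaks of the effectiveness of HOPS as a single thing.

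A reader might infer that the primary contrast simply has an 11–14% chance of a false efficacy claim. The documents do not support that, for three reasons:

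- The range counts significant results in either direction, and a result showing HOPS to be worse cannot support efficacy. The favourable-only figures are about half as large, although the relative inflation is the same.
- It assumes that one positive measure out of six is enough. The article never says so, and Hypothesis 1 joins its outcomes with "and".
- The lower end rests on an assumed correlation; higher values bring the figure below 11%.

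A reader might also infer that organizational skills should be the sole primary domain. The article does not settle this. Aim 1 classes homework performance as proximal too, and homework management is one of the three HOPS components.

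Finally, Bonferroni is valid, so the Holm point is an improvement and not the correction of an error. Holm lacks Bonferroni's simple matching simultaneous intervals, but the article plans none for these outcomes.

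**Conclusion.** The point holds in a limited form. The stated rule controls error at 5% per domain and does not control it for an overall claim that HOPS-ST is effective. If any single measure could carry such a claim, the two-sided rate under the global null is about 14% (independent), 11% (r = 0.5) or 7.5% (r = 0.8). The matching rates for results favouring HOPS are about 7%, 5.6% and 3.8%, against 2.5%. These figures rest on two-sided tests, equal correlations and an any-one-of-six rule that the article neither states nor excludes. If conclusions are kept strictly to each domain, there is no inflation to repair, only a sentence to add.

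Separately, Holm within each domain gains about 5 percentage points of power per measure and 9 for both measures (assuming 80% power each at 0.025 and r = 0.5) without weakening error control. The matter should be addressed, but it does not invalidate the design.

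**What to change.** 1. In the analysis section for Aims 1–3, replace the fixed 0.025 with Holm within each domain: the smaller p-value at 0.025 and, if significant, the larger at 0.05. The existing power calculation at 0.025 can stay, since it matches Holm's first step.

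2. In the same section, choose one of two statements for HOPS-ST vs TAU/WL:
   - conclusions are drawn separately for each domain, and a single positive measure will not be reported as overall efficacy; or
   - a named domain, or a fixed order of testing the domains, decides the primary aim and the other results are supportive.

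3. Make the reference to primary outcomes in the power paragraph agree with that choice.

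Both parts are needed, because Holm alone does not change the six-test rate. The cost is wording; no new data are required. Under the first statement the trial gives up a headline claim based on one measure. Under the second, a positive result outside the deciding domain or order cannot carry the primary aim. Timing matters for the second: enrolment was due to end on 28/02/2026, the article is dated 2026-06-11, and the study team knows the assignments. A deciding domain or order must therefore be fixed, and dated, before outcome data are examined. If that is no longer possible, the domain-by-domain statement is the safer choice.

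### Fixed Bonferroni at .025 for both measures in each domain is valid, but Holm's step-down has the same 5% within-domain error, never loses a rejection, and is more powerful for the second measure

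*Protocol article*

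**What the plan says.** The section on analyses for Aims 1–3 groups the outcomes into organizational skills, homework performance and academic achievement, and says "we will use a Bonferroni-adjusted significance level to correct for multiple comparisons within each domain". It then gives the level: "the significance level will be adjusted to.025 per domain for the two measures of organizational skills (COSS-P, COSS-T"), with the same treatment for "the two measures of homework performance (HPC, HPQ-T), and the two measures of academic achievement (APS, academic grades"). The power paragraph in that section also takes .025, described as "reflecting the Bonferroni corrected significance level to accommodate multiple testing of two outcomes for each outcome domain". Together these mean a family of two measures per domain, a family level of 5%, and each measure always judged at .025.

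No sequential procedure is mentioned. No reason is given for a single-step rule, and no simultaneous confidence intervals that would need one are promised for these aims. The article does not say whether a domain counts as won on one measure or only on both.

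**The concern.** With two tests, Bonferroni keeps the second at .025 even after the first has been rejected. Once one null hypothesis in a pair is rejected, only the other is still in play, and it can be tested at .05 without exceeding 5% for the pair. Holm's procedure does this. A measure with p between .025 and .05, whose partner has p of .025 or less, is called non-significant under the plan although the same error guarantee would allow a rejection.

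The organization domain is where this most plausibly matters. In the large prior trial described in the Introduction, caregiver-rated organization effects were d = 0.79 to 1.14 and teacher-rated effects 0.53 and 0.55. COSS-P is therefore likely to pass first, leaving COSS-T as the measure at risk. The enrolment target has also been cut from 240 to 135, so power is scarcer than first planned.

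**Working it through.** **Inputs from the protocol (power paragraph, Aims 1–3).** "schools (20 assigned to HOPS, 10 assigned to TAU"); "ICC = 0.04 (based on [4"]); R² = 0.60 at both levels, "which is the proportion of variation in outcomes explained by student and school-level covariates"; α = .025; 122 students after attrition; and "This sample size will result in a MDES of 0.48 with adequate power (80"%). **Assumed, because not stated:** two-sided tests, 28 df (30 schools − 2), and correlation between the two test statistics of 0.2 to 0.5.

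**1. The level.** 0.05 / 2 = 0.025, as stated.

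**2. The MDES.** Take one HOPS provider group against TAU/WL, with 122/30 = 4.07 students per school. Half the students in 20 HOPS schools gives 40.7, and 10 TAU/WL schools give 40.7.

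SE² = 0.04 × 0.40 × (1/20 + 1/10) + 0.96 × 0.40 × (1/40.7 + 1/40.7) = 0.0024 + 0.0189 = 0.0213, so SE = 0.146.

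Multiplier = t(0.9875; 28) + t(0.80; 28) = 2.368 + 0.855 = 3.223.

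MDES = 3.223 × 0.146 = 0.47, close to the stated 0.48. (All HOPS students pooled would give 0.42.)

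**3. Standard error used below.** To stay with the protocol's own figure, SE = 0.48 / 3.223 = 0.149. Critical values are 2.368 at .025 and 2.048 at .05.

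**4. The two rules.** Bonferroni rejects measure i if p_i ≤ .025. Holm rejects the smaller p if ≤ .025 and then, only if that succeeded, the larger if ≤ .05. Results come from noncentral-t power and simulation of correlated pairs.

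| True effects | Quantity | Bonferroni | Holm |
|---|---|---|---|
| 0.48 and 0.48 | power, each measure | 80% | 85–86% |
| 0.48 and 0.48 | power, both measures | 65–68% | 77–78% |
| 0.48 and 0.48 | power, at least one | 92–94% | 92–94% |
| COSS-P 0.80, COSS-T 0.53 | power, COSS-T | 88% | 93% |
| COSS-P 0.80, COSS-T 0.40 | power, COSS-T | 63% | 74% |
| COSS-P 0.80, COSS-T 0.30 | power, COSS-T | 38% | 49% |
| 0 and 0 | any false rejection | 4.7–4.9% | 4.7–4.9% |
| COSS-P 0.80, COSS-T 0 | false rejection of COSS-T | 2.5% | 5.0% |

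In the first block, the lower joint power goes with correlation 0.2 and the higher with 0.5. No simulated trial was rejected by Bonferroni and not by Holm.

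**5. Status of the effect sizes.** The 0.48 is the protocol's MDES, and 0.53 is a teacher effect it reports. The 0.80 is an assumption near the low end of the reported caregiver range. The 0.40 and 0.30 are assumptions below anything reported from the large trial. The reported effects concern separate aspects of organization, while the plan analyses COSS total scores.

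**The case against.** The strongest reply is that nothing here is an error. Fixed Bonferroni controls the error it claims to control, is prespecified, and agrees with the power calculation. That stands: a reader might infer that the analysis is invalid or the sample size miscalculated, and the documents support neither. Holm's first step is still .025, so the MDES holds.

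Three further limits stand.

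- **Not shown for every domain.** A reader might infer that power is thrown away on a weaker measure in all three domains. The caregiver–teacher gap is documented only for organization. The large trial's teacher effect on homework is not given, and neither academic measure has a reported d or is caregiver-rated.
- **Modest at the reported effect.** At 0.53, COSS-T already has 88% power. Gains of 11–12 points need effects of 0.30–0.40.
- **Not entirely free.** With COSS-P truly effective and COSS-T null, false rejection of COSS-T doubles to 5%. The case is realistic, since the early study delivered by school professionals found no improvement on teacher ratings. It remains within the 5% family level.

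Timing also counts. Enrolment was to close on 28/02/2026 with post-treatment about four months later, the article is dated 2026-06-11, and the team knows the assignments. A move to a more permissive rule must visibly precede analysis.

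What does not stand is that the choice is mere preference: Holm keeps every Bonferroni rejection at the same family level, and the protocol gives no reason that requires the single-step rule.

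**Conclusion.** The point holds as a worthwhile efficiency gain, not as a correction of an error. When both effects equal the MDES, Holm adds about 5 points per measure and 10–12 points for showing both. At the teacher effect reported from the large trial it adds about 5 points on COSS-T, and more only if the true teacher effect is smaller than that. It adds nothing to the chance of at least one significant measure in a domain, so it matters for conclusions about individual measures or a requirement for both.

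The figures rest on the standard error implied by the stated MDES, two-sided tests, 28 df and an assumed correlation of 0.2–0.5. That Holm loses no rejection and holds 5% within the domain needs none of these assumptions. A reader might also infer that Holm would settle error across the three domains or the two HOPS contrasts against TAU/WL. It would not; applied within a domain, it leaves that question as it is.

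**What to change.** In the analysis section for Aims 1–3, replace the fixed .025 with Holm's step-down within each domain: smaller p-value at .025 and, only if significant, the other at .05. Report Holm-adjusted p-values: twice the smaller p, and for the other the larger of that value and its own p, each capped at 1. Record the change as a dated amendment before any outcome data are analysed, and state that this was so. If analysis has already begun, keep Bonferroni as the prespecified rule.

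The power paragraph can stay, since .025 is Holm's first step. The cost is a sentence of text and the amendment, with no new data. Simultaneous confidence intervals are less direct under Holm, but Bonferroni-level intervals can still be printed beside the adjusted p-values. The higher error on a null second measure, up to 5%, should be accepted knowingly.

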#### Analyses for Aim 4: Mediation.

We will use structural equation modeling (SEM) to conduct mediation analyses [40] to explre if the effect of HOPS on academic performance works through improved organizational skills. SEM approaches allow us to explore individual and multiple mediator relationships by positing a path model for each mediator variable. Applying this framework, the total intervention effect is decomposed into two components: natural direct effect (NDE = the effect of HOPS on students’ academic performance without mediation), and the natural indirect effect (NIE = the effect of HOPS that seems to proceed through improved organization skills). As a result, total effect of HOPS = NDE + NIE and a significant NIE implies that the effect of HOPS on academic performance works through improved organizational skills [41].

